**5) Analysis**

◎ Analysis

- Per protocol (if needed intention to treat will be used)

◎ EEG power spectra analysis

- 1^st^ EEG vs 2^nd^ EEG: to evaluate acute effect of celecoxib administration.

- 1^st^ EEG vs 3^rd^ EEG: to evaluate long-term effect of celecoxib administration

Variables between subjects (celecoxib vs. placebo) and within subject (1^st^ EEG vs 2^nd^ EEG, 1^st^ EEG vs 3^rd^ EEG) will be analyzed

◎ TMS analysis

- Before and after of 7-days of celecoxib administration. Variables between subjects (celecoxib vs. placebo) and within subject (before vs. after) will be analyzed

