**Study 1 (Figure)**

EEG will be performed at baseline just before celecoxib (400 mg) or placebo delivery at 9 AM, and EEG will be repeated at 1 PM, 4 hours after administration To evaluate the long-term effects of celecoxib, subjects will take celecoxib or placebo 200 mg twice a day for 7 subsequent days, and a third EEG will be conducted at 1 PM on the last day, 4 hours after the final dose

**
[figure not shown]
**

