**11) Method of analysis**

**Study1**

◎ Change of EEG power spectra by single dose or 7-day treatment of celecoxib or placebo

- Variables between subjects (celecoxib vs. placebo) and within subject (1^st^ EEG vs 2^nd^ EEG, 1^st^ EEG vs 3^rd^ EEG) will be analyzed by student-t test and paired-t test. Analysis of EEG data will consider frequency bands (alpha, delta, theta and beta) and locations (frontal, central and parietal) using repeated measures analysis of variance (rmANOVA). A two-sided 5% significance level will be used for all statistical differences.

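### In Study 1 the drug effect is attached to before/after EEG contrasts that also run from 9 AM to 1 PM, and the plan does not say that the comparison with placebo decides

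*Protocol*

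**What the plan says.** **Timing.** For Study 1, the detailed study methods place the first EEG "just before celecoxib (400 mg) or placebo delivery at 9 AM". The second follows the same day ("EEG will be repeated at 1 PM, 4 hours after administration"), and then "a third EEG will be conducted at 1 PM on the last day". These times apply to both arms.

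**Purpose of the contrasts.** Section 11, 5) Analysis pairs the first EEG with the second "to evaluate acute effect of celecoxib administration" and the first with the third for the long-term effect. The next sentence says that variables will be analysed both between subjects (celecoxib against placebo) and within subject.

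**Tests.** Section 11, 11) Method of analysis says that the Study 1 variables "will be analyzed by student-t test and paired-t test". It adds a repeated measures ANOVA for frequency bands and locations, and sets two-sided 5% throughout. The Study 1 primary end point is worded as a change in power spectra after the single high dose, without reference to placebo. The sample size section leaves the test as paired or unpaired.

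**Study 2.** The analysis section describes the TMS contrast as "Before and after of 7-days of celecoxib administration", again with between-subject and within-subject comparisons. The method section lists a paired t-test or Wilcoxon signed rank test, and repeated measures ANOVA for celecoxib against placebo. No clock times are given for the TMS sessions.

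**The concern.** Each before/after EEG contrast in Study 1 is also a contrast between 9 AM and 1 PM, and between a first and a repeat recording. Anything that moves the EEG between those occasions, apart from the drug, goes into the celecoxib arm's mean change, and a paired t-test in that arm cannot separate it from a drug effect. The placebo arm is recorded at the same clock times and would remove any shift that both arms share, but the paired test does not use it.

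The plan nevertheless gives the drug's name to these before/after contrasts. It runs paired and between-arm tests side by side at the same level and names neither as decisive. It also does not say that the Student t-test compares changes from baseline and not raw follow-up values. At stake is what counts as a positive result on the Study 1 primary end point. A significant paired test in the celecoxib arm could be reported as an acute drug effect under the plan's own labels, although the randomised comparison shows nothing.

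**Working it through.** **1. The plan's own figure.** The inputs from the sample size section are: difference 0.4, SDs 0.4 and 0.2, two-sided 5%, power 0.8.

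Unpaired formula: n per group = (0.4² + 0.2²) × (1.960 + 0.842)² / 0.4² = 0.20 × 7.849 / 0.16 = 9.81, so 10. The stated n is reproduced. A paired formula on the same SDs also gives 10 if the correlation is 0, and 8, 6 or 4 if it is 0.25, 0.5 or 0.75. The figure of 10 is not in error, but it does not show which test the trial was built around.

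**2. Set-up of the check.** Assume that celecoxib has no effect and that the mean change from baseline is the same shift in both arms. Write the shift as δ, in units of the SD of the within-subject change. The documents give no value for δ, so the values below are assumptions, and zero is included. Changes are taken as normal and independent, with 10 subjects per arm.

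**3. Paired t-test in the celecoxib arm.** The statistic has 9 df and noncentrality δ√10; the two-sided 5% critical value is 2.262. The rejection probability is P(|T| > 2.262).

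**4. Between-arm t-test on change.** The statistic compares the two mean changes on 18 df. A shared δ cancels, so the rejection probability should stay at 5%. Simulation (200,000 trials per value of δ) confirms this.

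| Assumed shared shift δ (SD of change) | Noncentrality δ√10 | Celecoxib paired test significant | Between-arm test on change significant |
| --- | --- | --- | --- |
| 0 | 0 | 5.0% | 5% |
| 0.3 | 0.95 | 13.6% | 5% |
| 0.5 | 1.58 | 29.3% | 5% |
| 0.75 | 2.37 | 56.2% | 5% |

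**5. Neither test decisive.** If a significant result on either the celecoxib paired test or the between-arm test were accepted as evidence of effect, simulation gives a false-positive rate of about 8% at δ = 0. The two tests share the celecoxib data, so this is below the 1 − 0.95² = 9.75% of two independent tests. Leaving the choice open therefore costs error control even with no time-of-day shift.

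**The case against.** The strongest reply is that the randomised comparison is in the plan. The sentence directly after the quoted line calls for celecoxib against placebo, the method section gives it a Student t-test, and both arms are recorded at the same clock times. The quoted line may only say which recordings serve the acute question and which the long-term one. Nowhere does the protocol say that a significant paired test in the celecoxib arm is enough, and a statistical analysis plan that is not shown may settle the order of the tests.

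Much of this stands. A reader might infer that the drug effect is to be read only from within-arm tests and that the placebo arm goes unused; the text does not support that. A reader might also assume a rule of celecoxib significant and placebo not; the protocol states no such rule, so its error rate is no charge against this plan. Regression to the mean is not a reason here either, since eligibility does not select on EEG or TMS values.

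Nor does the clock-time argument carry over to Study 2. No TMS clock times are given, and repeated measures ANOVA is named there for celecoxib against placebo.

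What the reply does not remove is that this protocol already assigns a meaning and a 5% test to the before/after contrasts. That goes beyond detail left for later: a stated test, labelled as the drug's effect, cannot isolate that effect.

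**Conclusion.** The point holds for Study 1 in this form: the before/after EEG contrasts are labelled as the acute and long-term effect of celecoxib, they are confounded with time of day and repeat recording, and the between-arm comparison that would remove a shared shift is planned but not made decisive or defined on change from baseline.

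The size is conditional. The inflation in the celecoxib paired test runs from none at zero shift to more than half of trials at 0.75 SD, and it depends wholly on a shift that the documents do not quantify. The figure of about 8% at zero shift needs no such shift, but does assume that either test would be accepted. All the figures assume normal changes, 10 analysed subjects per arm and a shift common to both arms.

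For Study 2 only a consistency remark remains, because its between-arm analysis is named but not stated to be the deciding one.

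**What to change.** 1. In section 11, 5) Analysis, restate the two EEG contrasts as second minus first EEG, celecoxib versus placebo (acute), and third minus first EEG, celecoxib versus placebo (long-term).
2. In section 11, 11) Method of analysis, state that conclusions on celecoxib's effect in Study 1 rest on the between-arm difference in change from baseline, and that the Student t-test is applied to that change.
3. Keep the within-arm paired results as supportive or descriptive only, for example as mean changes with 95% confidence intervals.
4. For consistency in Study 2, state that the group-by-time term of the repeated measures ANOVA, that is, the between-arm comparison of change, is the deciding one.

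The cost is protocol wording only. No visits, recordings or subjects are added, and the sample size figure can stand, since the unpaired formula reproduces it. The change should be made before the blinding codes are broken.

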**6) Point of distinction**

◎ Celecoxib has been studied in several in vivo epilepsy models, including acute seizures, spontaneous recurrent seizures, and kindling models. The majority of studies have indicated anticonvulsant or neuroprotective effects of celecoxib. However, there is no study on the electrophysiological effect of celecoxib in humans. This research will deepen our understanding about inflammation and neuronal activity and will be a basis of clinical study for utilizing celecoxib as an anticonvulsant in the future.

**7) Risk and benefit of subjects**

◎ Study drug

- Refer to instructions for detailed side effects. This medication is widely used to treat degenerative and rheumatoid arthritis, ankylosing spondylitis, and acute pain. In the large clinical trials before FDA approval and post market surveillance, stomach upset, facial swelling, abdominal pain, nausea, rash, diarrhea, insomnia may occur. However, in a study with 12 subjects, there was no serious side effect with 2400mg oral administration. As the study subjects are heathy adults, and the study drug is FDA approved and the dose of study drug is tolerable, the possibility of occurrence of side effect is very low. All study subject will be insured for in case of having any adverse events.

◎ Exams

- EEG is painless and safe.

- rTMS - rTMS is well-tolerated and associated with few side-effects. The common side effect is headahes but these are mild and generally diminish spontaneously.

**8) Dropout criteria**

Dropout could be decided at any time during the study period for the following reasons. If the patient had any drinks containing caffein (coffee, green tea, or energy drink) or took alcohol, when the subject does not wish to proceed with study drug administration or withdraws consent during the study period, in the cases where the subject requires to discontinue the investigational product or any case in which serious adverse event (SAE) or adverse drug reaction is observed, poor study drug compliance (<80%), when the subjects could not be undergone rTMS due to headache. the subject takes any medication that is expected to influence the safety and pharmacokinetic characteristics of investigational product, without permission of the investigator, when the major protocol deviation occurs such as subject found not to be eligible based on inclusion and exclusion criteria after enrollment.

**9) Adverse events (AEs)**

**◎ Definition of AEs**

An adverse event is defined as any unfavorable and unintended change in the structure, function, or chemistry of the body, or worsening of a pre-existing condition, temporally associated with the use of a product whether or not considered related to the use of the product or device. In this study, such changes will be monitored, and summarized.

**◎ Definition of Serious AEs**

ICH (International Conference on Harmonization) defined serious AE as below:

- resulted in death or is life-threatening,

- required inpatient hospitalization or prolongation of existing hospitalization,

- resulted in persistent or significant disability/incapacity,

- resulted in a congenital anomaly/birth defect.

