**2) Exclusion criteria**

1. Healthy male or female aged between 20 and 50 years.

2. Body mass index between 16.0 and 30.0 kg/m2.

Exclusion criteria

1. History of cardiovascular disease (heart disease, stroke)

2. History of hepatic disease

3. History of gastrointestinal hemorrhage or inflammatory bowel disease

4. History of seizure (epilepsy)

5. History of any kind of medication within 1 week before screening

6. History of hypersensitivity to any medication

7. Females who were pregnant, breastfeeding, or intended to become pregnant

8. Presence of clinically significant electrocardiogram abnormality at screening

9. Aspartate aminotransferase (AST) or alanine aminotransferase (ALT) greater than 2.0 × the upper normal limit

10. Serum creatinine levels greater than 1.5 × the upper normal limit

11. Hyperkelamia, K level ≥ 5.5 mmol/L

12. Galactose intolerance

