**◎ Report of AE**

At Visit 2, Study personnel will directly observe study subjects for 30 minutes after taking study drug for immediate reactions. The subjects also observed during TMS procedure and until 30 min after examination. Study personnel will ask the degree of pain (Visual analogue scale) immediately after TMS. The occurrence and severity of any AE by study drug or device during this visit will be recorded on the appropriate CRF. The subjects will be asked to note and characterize in their own words about any local or systemic AEs they experience, during 7-day period between visit 2 and 3.

At visit 3, study subjects will be queried regarding the occurrence of any SAE or other unexpected AE that may have occurred since the last visit. These events will be recorded on the CRFs.

The reporting period for AEs is the period starting from the time of administration of study drug to the day of study completion (visit 3).

Events that involve a death or are unexpected, serious and related or possibly related to the investigational drug will be submitted to the Pfizer Inc. within 24 hours of discovery. In case blinding code inevitably needs to be broken for treatment of subject, investigator must report it to the Pfizer Inc. within 24 hours of discovery.

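### The serious-AE definition is a closed list of four criteria with no medical-judgement criterion, so some medically important non-fatal events are non-serious by default and fall outside 24-hour submission

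*Protocol*

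**What the plan says.** All references are to the Protocol.

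- **Section 11, 9), Definition of Serious AEs.** The lead-in is "ICH (International Conference on Harmonization) defined serious AE as below". Four items follow: "resulted in death or is life-threatening"; "required inpatient hospitalization or prolongation of existing hospitalization"; "resulted in persistent or significant disability/incapacity"; and "resulted in a congenital anomaly/birth defect". The list ends there. It has no wording that marks the items as examples and no clause for medical judgement.
- **Section 11, 9), Report of AE.** The 24-hour route to the funder is for "Events that involve a death or are unexpected, serious and related or possibly related to the investigational drug". A second 24-hour duty concerns breaking the blind. The AE reporting period runs from study drug administration to visit 3.
- **Section 11, 9), Action taken.** Medical intervention is code 3 and hospitalization is code 5, so they are separate outcomes.
- **Section 10, 2), Exclusion criteria.** These include "History of seizure (epilepsy"), gastrointestinal haemorrhage and hypersensitivity to any medication.
- **Study Summary, Adverse effect evaluation.** Every adverse event after enrolment is recorded, whatever its cause.
- **Section 12, Basic principal.** The trial undertakes to follow ICH E2A on safety definitions and expedited reporting.

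**The concern.** The four criteria turn on outcome or on admission. An event can need prompt treatment and matter a great deal in a healthy volunteer, yet meet none of them. The protocol foresees events of this kind, because it codes medical intervention apart from hospitalization. It also treats seizure, gastrointestinal haemorrhage and drug hypersensitivity as relevant risks, because it excludes people with a history of them.

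The definition matters because the 24-hour rule depends on it. For any non-fatal event, being serious is a necessary condition for submission. If the definition leaves an event out, the reporting rule leaves it out too, whatever its relation to the drug and however unexpected it is. At stake is how soon the funder learns of an important reaction in a study whose subjects are healthy.

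**Working it through.** No arithmetic applies to the definition itself. The check sets the definition, the reporting rule and the rest of the safety text side by side.

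**Step 1. Is there a judgement criterion anywhere else?** The other parts of section 11, 9) cover the general AE definition, severity grades, causality, action taken and reporting. Section 11, 10) covers monitoring. None adds a criterion for seriousness. The severity scale has a top grade for incapacitating events, but nothing links that grade to seriousness.

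**Step 2. Apply the four criteria.** Take a non-fatal event that is possibly drug-related and treated without admission. Assume that it does not threaten life and leaves no lasting or significant disability.

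| Criterion | Gastrointestinal bleed, outpatient care | Hypersensitivity reaction treated on site | Self-limited convulsion |
| --- | --- | --- | --- |
| Death or threat to life | no | no | no |
| Admission or longer stay | no | no | no |
| Disability | no | no | no |
| Congenital anomaly | no | no | no |
| Serious as written | no | no | no |

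**Step 3. Apply the 24-hour rule.** For a non-fatal event the rule is: submit if serious AND unexpected AND at least possibly related to the investigational drug. With the first condition false, the other two do not matter. The event is recorded on the case report form and is not submitted within 24 hours.

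**Step 4. Apply the rule after a judgement criterion is added.** The three events can now be judged serious. Submission still needs the other two conditions:

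- *Unexpected.* Section 11, 7) refers to the product instructions for side effects and names several, among them rash and facial swelling. It does not name bleeding or convulsion. A hypersensitivity reaction that shows itself as rash or swelling might be held to be expected. Expectedness of a bleed is not stated.
- *Drug-related.* A convulsion attributed only to TMS fails this condition however seriousness is defined.

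The added criterion therefore removes one barrier and does not guarantee submission.

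**Step 5. Size.** The definition governs 20 + 20 = 40 subjects. Study 2 plans 20 subjects x 2 sessions = 40 TMS sessions. The baseline session comes just before the first dose, so 20 sessions precede the AE reporting period, and the causality table classes an event before drug intake as not related. That leaves 40 - 20 = 20 planned sessions after dosing. The documents give no event rate, so no expected count can be derived.

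**The case against.** The strongest reply is that section 12 already binds the trial to ICH E2A on both definitions and expedited reporting, so the short list does no harm. This stands in part: it means one cannot say that such an event could never be expedited. It does not remove the defect. The AE section presents its four items as the ICH definition, so site staff would take them as the whole test, and a general sentence under ethics gives them no other working criterion. What E2A contains is not in the documents. A reader might infer that the protocol misquotes ICH, but that cannot be shown from the text and the point does not need it.

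A second reply is that lack of admission does not by itself make an event non-serious. That is right. An investigator may judge a bleed or a convulsion life-threatening or disabling. The gap is confined to events that are neither, as Step 2 assumes.

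A third reply is that existing safeguards suffice. All events are recorded, subjects are watched during TMS and for 30 minutes afterwards, and the principal investigator reviews data on recruitment of every 10 subjects. So no event is lost, but none of these is an expedited route for the event.

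A reader might also infer that the list keeps a TMS-provoked convulsion out of expedited reporting. The documents do not support that as the effect of the list alone, because the drug-relatedness condition excludes such an event with or without the added criterion. Nor do they support saying that an event would drop out of a serious-AE summary or escape a trial-level halt: the protocol states no such summary and no halt rule keyed to seriousness.

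**Conclusion.** The point holds in a limited form. The definition is closed at four criteria, and being serious is necessary for 24-hour submission of any non-fatal event. A possibly drug-related event that needs treatment but meets none of the four is non-serious by default and is only recorded.

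The conclusion rests on reading the AE section as site staff would, with its list as the complete test, and on the event being neither life-threatening nor disabling. It concerns the timeliness of safety reporting for 40 subjects. Frequency is unknown from the documents and may well be low. The change is worth making before the study starts because it is cheap and the subjects are healthy volunteers.

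**What to change.** 1. Add one criterion to Definition of Serious AEs: an event is also serious if, in the investigator's judgement, it is medically important because it may jeopardise the subject or need intervention to prevent one of the listed outcomes.
2. State in Report of AE that the term serious has this meaning.
3. Reconcile both subsections with the E2A commitment in section 12, so that the AE section and the ethics section point to the same definition.

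The dropout criteria in section 11, 8) are clinical management and are left as they are. The change does not create a route for events attributed only to TMS.

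The cost is about one line in the protocol, a matching entry on the serious-AE form, and possibly one or two more serious-AE reports. No endpoint, sample size or analysis changes.

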**◎ Assessment method for severity of AE**

| 1 = Mild | Awareness of signs or symptoms, but easily tolerated; is of minor irritant; causing no loss of time from normal activities |
| --- | --- |
| 2 = Moderate | Discomfort severe enough to cause interference with usual activities |
| 3 = Severe | Incapacitating with inability to work or do usual activity |

**◎ Causality assessment**

| Causality | Assessment criteria |
| --- | --- |
| Not related | Event before taking the drug  Event or laboratory test abnormality, with a time to drug intake that makes a relationship improbable  Definite other plausible explanations |
| Doubtful | Event or laboratory test abnormality, with a time to drug intake that makes a relationship improbable (but not impossible)  Disease or other drugs provide plausible explanations |
| Possible | Event or laboratory test abnormality, with reasonable time relationship to  drug intake  Could also be explained by disease or other drug  Information on drug withdrawal may be lacking or unclear |
| Probable | Event or laboratory test abnormality, with reasonable time relationship to  drug intake  Unlikely to be attributed to disease or other drugs  Response to withdrawal clinically reasonable  Rechallenge not required |
| Very likely | Event or laboratory test abnormality, with plausible time relationship to  drug intake  Cannot be explained by disease or other drugs  Response to withdrawal plausible (pharmacologically, pathologically)  Event definitive pharmacologically or phenomenologically (i.e. an  objective and specific medical disorder or a recognised pharmacological  phenomenon)  Rechallenge satisfactory, if necessary |

